### 4.3 Exclusion criteria

Exclusion criteria are:

- Progressive phenotype of MS
- Relapse (treated or untreated with steroids) < 6 weeks before start study.
- Abnormalities of vitamin D hormonal system other than low dietary intake or limited sun exposure (i.e. Malabsorption, Cirrhosis, Nephrotic syndrome, Hyperthyroidism, Renal failure, Rickets, hypoparathyroidism, known malignancy, granulomatous disorders (TB, Sarcoidosis, Silicosis), and lymphomas)
- Intake of drugs that influence vitamin D homeostasis other than corticosteroids (i.e. Orlistat and anticonvulsants).

- Conditions associated with an increased susceptibility for hypercalcemia (known arrhythmia or heart disease, treatment with digitalis or hydrochlorothiazide, and those who suffer from nephrolithiasis).
- Frequent use of tanning bed (> 1 time/week).
- Alcohol or drug abuse
- Pregnancy or the intention to become pregnant during the study period.

#### 4.4 Sample size calculation

We use the preliminary data of the study 'Vitamin D and the T cell compartment in multiple sclerosis' (NL 22666.096.07) for the power calculation. The inserted graph shows the relationship between Treg function and serum 25(OH)D levels in our previous study. In our suppression assay, we cultured Treg and responder T cells (Tresp) in different ratios (Treg/ Tresp 1:4 = 0.25). The Treg/Tresp ratio at which 50% suppression of Tresp proliferation was achieved, was set as ED50. We found that ED50

[figure not shown]

Linear Regression

correlated negatively with serum 25(OH)D values; i.e. that Tregs were more able to suppress T cell proliferation in patients with high 25(OH)D levels.

In the cohort with serum 25(OH)D levels below 100 nmol/L, mean ED50 was 1.0413 (SD 0.5503). This means that in the proliferation suppression assay, the Treg/Tresp ratio had to be approximately 1:1 to achieve 50% suppression of Tresp proliferation compared with the proliferation of stimulated Treg alone. In the study which

has been conducted with vitamin D therapy at a dose of 250 µg/d, 25(OH)D levels were elevated to a mean of 413 nmol/L (Burton et al). Therefore we can expect (if the correlation we found can be modified by vitamin D therapy) the Treg/Tresp ratio to be very low. The culture condition with the lowest Treg/Tresp concentration that we use is 1 Treg on 4 Tresp (corresponding ED50: 0.25). When we take this value as a target for our primary endpoint, the expected difference is  $1.0413 - 0.25 = 0.7912$ . Together with an power of 80% and alpha of 0.05, this results in the following formula for 2-sided significance:

$$N = (2\alpha + 2\beta)^2 \times (2 \times SD^2) / (\text{exp difference})^2 = (1,96 + 0,84)^2 \times (2 \times 0,5503)^2 / (0,7912)^2 = 7,84 \times 1,93502 \approx 15 \text{ patients needed.}$$

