### **8.2 Univariate analysis**

The effect of the intervention on T cell characteristics (primary outcome measures) will be expressed as the difference between the respective continuous variables (ED50, T cell subsets or Th1/Th2 ratios) before and after treatment. The significance of this difference will be tested with a paired non-parametrical test (Wilcoxon ranking test). The same holds for the effect of the intervention on safety parameters and vitamin D metabolite values.

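### The sample-size line in section 4.4 squares the factor 2: the formula as written gives 8 patients, not 15, and the SD of within-patient change that the paired test needs is not stated

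*Protocol*

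**What the plan says.** Protocol section 4.4 takes its inputs from an earlier study. In patients with 25(OH)D below 100 nmol/L, "mean ED50 was 1.0413 (SD 0.5503"). The post-treatment target is 0.25, the lowest Treg/Tresp ratio cultured, so the expected difference is "1.0413 - 0.25 = 0.7912". The error rates are introduced with "Together with an power of 80% and alpha of 0.05, this results in the following formula for 2-sided significance".

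The formula in symbols contains ("2 \times SD^2) / (\text{exp difference})^2". The line with numbers then reads ("2 \times 0,5503)^2 / (0,7912)^2 = 7,84 \times 1,93502 \approx 15", and the section concludes that 15 patients are needed.

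Sections 3 and 6.2 describe a single arm without randomisation. Section 8.2 expresses the effect on ED50 as the difference before and after treatment: "The significance of this difference will be tested with a paired non-parametrical test (Wilcoxon ranking test"). Section 6.5 says that withdrawn patients are replaced.

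**The concern.** The symbols and the numbers in section 4.4 do not agree. In symbols the 2 multiplies SD²; in numbers it sits inside the square. The two versions differ by a factor of two, and the 15 comes only from the second.

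A separate gap concerns the SD. The expression 2 × SD² with a between-patient SD is the familiar per-group formula for comparing two independent groups. This trial compares each patient with himself or herself, so its precision depends on the SD of the change. Section 4.4 gives neither that SD nor a correlation between visits from which it could be derived.

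Section 4.4 is the only justification for the number of patients exposed. An ethics committee reading it is told that 15 are needed for 80% power, and that does not follow from the stated inputs.

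**Working it through.** **Inputs, all from section 4.4:** two-sided alpha 0.05 and power 80%, so (1.96 + 0.84)² = 7.84; SD = 0.5503; difference = 0.7912. (Exact subtraction gives 0.7913, which is immaterial.)

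**1. The protocol's figure, as substituted.**
- (2 × 0.5503)² = 1.2113 and 0.7912² = 0.6260
- 1.2113 / 0.6260 = 1.93502, the intermediate value that the protocol prints
- 7.84 × 1.93502 = 15.17, printed as about 15

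The match to five decimals shows that the 2 really was squared in the calculation. It is not a typesetting or PDF artefact.

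**2. The formula as written in symbols.**
- 2 × 0.5503² = 0.6057
- 0.6057 / 0.6260 = 0.9675
- 7.84 × 0.9675 = 7.59, so 8 patients

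**3. Relation to the paired design.** With the same SD at both visits and correlation ρ between them, SD_change = SD × √(2(1 − ρ)), and the normal-approximation size is N = 7.84 × SD_change² / difference². At ρ = 0, SD_change² = 2 × SD², and step 2 is reproduced exactly. At any other ρ the answer changes. The documents give no ρ, so the values below are assumptions.

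| Assumed ρ | SD_change | N, normal approximation | N for 80%, paired t |
|---|---|---|---|
| −0.5 | 0.953 | 11.39 | 14 |
| 0 | 0.778 | 7.59 | 10 |
| 0.5 | 0.550 | 3.80 | 6 |

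**4. What 15 completing patients give under the planned test.** Exact two-sided Wilcoxon signed-rank test, simulated with normally distributed differences:

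| Assumed ρ | Power for 0.79 | Mean ED50 reduction with 80% power |
|---|---|---|
| −0.5 | about 83% | about 0.76 |
| 0 | about 94% | about 0.63 |
| 0.5 | over 99% | about 0.44 |

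The paired t-test reaches 80% power with 15 patients at slightly smaller reductions, 0.61 (ρ = 0) and 0.43 (ρ = 0.5). At those reductions the Wilcoxon test has only about 78% power, so the t-test values should not be quoted for this plan.

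**5. What would make the printed 80% true.** For 15 patients to have just 80% power at 0.79, the SD of change would have to be about 1.02 (paired t), which is 1.02 / 0.5503 ≈ 1.85 times the stated SD. Nothing in section 4.4 suggests this.

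**The case against.** The strongest defence is that nothing in the conduct of the trial goes wrong. The slip errs on the safe side: at every correlation examined from −0.5 to 0.5, 15 patients have at least 80% power for 0.79, and the remedy leaves the number at 15. That stands, and it limits the weight of the point.

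A reader might count the two-group form as a second numerical error. It is not one. At ρ = 0, 2 × SD² is exactly the variance of the change, so the paired formula also returns 7.59. What remains is an assumption that the protocol leaves unstated, and its numerical effect cannot be fixed from the documents.

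Other stronger readings are tempting but not supported:

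- **That 0.79 is the largest change the assay can record.** Section 4.4 says only that 1:4 is the lowest ratio cultured. It does not say that ED50 cannot be extrapolated below it. A hard floor would also conflict with an SD of 0.5503 at the second visit: with a mean of 0.25, a normal distribution would put half the values below that floor.
- **That a null result would be misread.** The 80% is tied to 0.79. If power there is higher, a null result is stronger evidence against 0.79. Power for smaller effects is a separate question, which the slip does not raise.
- **That 15.17 should have become 16.** The value comes from the slip, so rounding it differently corrects nothing.

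It could also be said that 15.17 is the total for a two-arm trial, 2 × 7.59. The arithmetic is right, but the trial has one arm.

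**Conclusion.** The error is real and can be shown from section 4.4 alone. The factor 2 is squared in the substitution and doubles the answer from 7.59 (8 patients) to 15.17. The statement that 15 patients are needed for 80% power therefore does not follow from the protocol's formula and inputs. In addition, the SD of within-patient change is neither given nor stated as an assumption, although the planned test depends on it.

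The consequence is limited. A reader might infer that the trial is too small for its target; the figures show the opposite. Power for 0.79 with 15 completers is about 94% at ρ = 0, over 99% at ρ = 0.5 and about 83% at ρ = −0.5. These figures assume SD 0.5503 at both visits and normally distributed differences, and the documents confirm neither.

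The text should be corrected because it is the stated basis for the number of patients exposed. It is not a defect that invalidates the design or the analysis.

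**What to change.** Keep 15 patients and rewrite the calculation in section 4.4:

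1. Use the paired form, N = (Z for alpha + Z for beta)² × SD_change² / difference², without squaring the 2.
2. State the assumed SD of within-patient change, or the assumed correlation between visits, and label it as an assumption. If the earlier study holds repeated ED50 measurements, take it from there.
3. Replace the claim that 15 patients are needed for 80% power with what 15 completing patients provide under the Wilcoxon signed-rank test. For example: with SD 0.5503 at both visits and normal differences, power for a mean ED50 reduction of 0.79 is about 94% if the visits are uncorrelated, over 99% at a correlation of 0.5 and about 83% at −0.5; 80% power is reached at a reduction of about 0.63 (correlation 0) or 0.44 (correlation 0.5).

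The cost is a rewording of one section by amendment. Patient numbers, procedures and the analysis in section 8.2 stay as they are, and the replacement rule in section 6.5 already aims at 15 completers.

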## 5. TREATMENT OF SUBJECTS

### 5.1 Investigational product/treatment

The subjects will be supplemented with Vigantol® oil. This is a commercially available (Merck™) oil-based solution of vitamin D3 in a concentration of 500 µg/ mL. We purchase the product directly from the company, which ensures quality control. The patients will have to take 1 ml of the solution at breakfast. The pipette which is enclosed with the bottles can be used to dose the drops. The patients has to drop 40 drops on a spoon. The product is tasteless and can be taken with any other food product.

Vigantol® is registered as a medicine in Germany to prevent vitamin D deficiency in healthy people without resorption disorders, and to supplement vitamin D in vitamin D deficiency (see enclosed 'fachinformation' or product information (SPC)). In the Netherlands, vitamin D is not registered as a medicinal product and is regarded as a supplement (Dutch: voedingssupplement). It is in this study not used to treat any disease, but merely to additionally support the daily intake of participants by food and sun exposition to a higher level.

### 5.2 Use of co-intervention

Patients who take part in this study are treated with interferon beta 1a (Rebif®) or Interferon Beta 1b (Betaferon® or Avonex®) and have to continue this treatment. When taking multivitamin supplements, they can be continued when the incorporated amount of vitamin D does not exceed 5 µg/day. Excessive eating of products which contains lots of calcium (dairy products) or vitamin D (fat fish and cod liver oil, in lesser amounts meat, eggs, dairy products, avocado) should be discouraged. As part of the routine visits at week 1, 6 and 12, the calcium and vitamin D intake will be inventoried. Also, the amount of sunlight exposure and recent sun-vacations will be assessed. In case of a relapse of MS during the study period, this can be normally treated with corticosteroids.

### 5.3 Escape medication

There is no escape medication for vitamin D. There is no evidence-based cut-off value for hypervitaminosis D. Vitamin D levels are too high when calcium metabolism starts to decompensate and serum levels of calcium rise to pathological levels (serum total calcium >2.60 mmol/L). In adults with a normal parathyroid function, this only happens at daily vitamin D intakes of 1.000–2500 µg/ day (40.000–100.000 IU) (See SPC Vigantol®). We supplement our patients with only 500 µg/ day (20.000 IU). Although whole-day-long total-body sun-exposure

could theoretically provide the equivalent of 250 µg vitamin D intake, the total intake stays still well below the intake needed to develop hypercalcemia.

Several studies support the safety of supplying high doses of vitamin D to MS patients. Vigantol® has been used to supplement children with vitamin D (Maalouf J, et al. 2008). There were no side effects reported. One study supplemented to 12 MS patients the equivalent of 1.000 µg/d (40.000 IU) in weekly boluses of 7.000 µg (280.000 IU) for 28 weeks. The mean serum 25(OH)D level at study termination was 325 nmol/L (min-max range 200-800 nmol/L) (Kimball et al. 2008).

Another study supplemented to 24 MS patients 250 µg/d (5.000 IU) for 52 weeks. The maximum mean 25(OH)D was 413 nmol/L (min-max range 66-720 nmol/L) (Burton et al. 2008). In both studies, no decompensation of calcium metabolism (serum total calcium and urine Ca2+/creatinine rate) was observed and no side effects were reported.

Therefore, the risk of our intervention to decompensate calcium metabolism and to elicit a hypercalcemia is very low. However, to supply vitamin D as safe as possible, we will follow our patients intensively. The first 6 weeks of the study, we do regular blood tests and instruct the patients to contact their neurologist if any side-effect occur. Potential side effects of hypercalcemia include: nausea, vomiting, diarrhoea, constipation, anorexia, apathy, pain in head, pain in muscles or joints, muscle weakness, sleepiness, uraemia (tiredness, decreased libido), polydypsia (excessive thirst), or polyuria (passage of large volumes of urine) (see SPC Vigantol®). When patients report these complaints, serum total calcium levels will be checked additionally.

In the unlikely case that hypercalcemia occurs in the current regimen, the vitamin D supplementation has to be stopped. Normalisation of serum calcium will be fastened by applying calcium-free nutrition, and promoting an excessive fluid intake. Eventually, a forced diuresis by furosemide can be applied. In case of a very severe hypercalcemia, subjects with a normal kidney-function can be given isotonic NaCl-solution (3-6 l/24h) to wash out the calcium. In case of oligo- or anuria, hemodialysis might be indicated.

## 6. METHODS

### 6.1 Study parameters/endpoints

#### 6.1.1 Main study parameter/endpoint

The main study endpoint is the function of regulatory T cells (CD4+CD25+CD127) in the T cell compartment. This will be assessed by testing their capability to inhibit CD3-driven Tresp (CD4+CD25) cell proliferation in culture.

#### 6.1.2 Secondary study parameters/endpoints (if applicable)

Several other T cell characteristics of the T cell compartment will also be investigated. The number of regulatory T cells in the circulation, as well as the percentages of individual T helper cell subsets within the CD4+ T cell compartment will be determined by flow-cytometry.

Several parameters will be assessed to investigate the safety of vitamin D3 supplementation. These are:

- Plasma levels of total calcium, albumin and parathyroid hormone (PTH) to assess a potential decompensation of calcium metabolism.
- Plasma levels of phosphate, potassium, sodium, creatinine and urea to assess a potential decompensation of kidney function.
- Plasma levels of aspartate aminotransferase (AST), alanine aminotransferase (ALT), alkaline phosphatase (AP) to assess a potential decompensation of liver function.

The elevation of serum 25(OH)D and 1,25(OH)2D levels will be measured to assess the effectiveness of the intervention.

### 6.2 Randomisation, blinding and treatment allocation

This pilot study has only one arm. All participants receive the same intervention and are not randomised.

### 6.3 Study procedures

[figure not shown]

The study is outlined in the figure presented above (time in weeks). At inclusion, patients will be assessed with a standard CRF (see attachment), to check the in- and exclusion criteria. If the patient matches the inclusion criteria, and is willing to sign the informed consent form, he or she will be included in the study.

At the baseline visit, blood will be collected to assess baseline-values before intervention. Herefore, 8 tubes of blood will be drawn by an experienced research nurse. The subjects will receive the Vigantol® for the first 6 weeks of the study (5 flacons à 10 ml) and instructions on how to dose and use the pipette. Additionally, exposure to vitamin D by diet and sunlight exposure and exposure to calcium by diet will be assessed. The patient takes the following dose:

|          |          |        |          |                               |
|----------|----------|--------|----------|-------------------------------|
| Week 1-6 | 500 µg/d | 1.0 ml | 40 drops | total 42.0 ml                 |
|          |          |        |          | Total week 1-6 50.0 ml |

Appointments will be made for the blood controls at week 2 (2 tubes), 4 (2 tubes) and 6 (2 tubes). When coming for a blood monster in the hospital, a short standardised contact with a research nurse will be arranged to assess side-effects and promote compliance. At the

control appointment at week 6 of the study, the amount of Vigantol left in the bottles will be checked, to assess compliance objectively. Dietary intake by calcium and vitamin D and sunlight exposure will be assessed. The remainder of the Vigantol to complete the study will be provided (5 flacons à 10 ml), and the control appointments at week 12 and 16 will be made.

|                                |          |        |          |               |
|--------------------------------|----------|--------|----------|---------------|
| Week 7-12                      | 500 µg/d | 1.0 ml | 40 drops | total 42.0 ml |
| Total week 7-12 50.0 ml |          |        |          |               |

At the appointment at week 12, the remainder of Vigantol in the bottles will again be assessed. Additionally, calcium and vitamin D intake will be assessed. At this time-point, a total of 7 tubes of blood will be collected to assess the T cell characteristics.

After completing the study protocol in week 12, patients will immediately stop vitamin D3 therapy. A last control is at week 16 to check the biochemical markers and wellbeing of the patient. After this last control, patients are allowed to continue vitamin D supplementation, however it is advised to restrict to the doses indicated by the report of the Dutch Health Counsel (Health Counsel of the Netherlands, 2008), in which supplementation with 20 µg/day is indicated for patients at risk for an impaired vitamin D status. For this purpose, commercially available vitamin D3 tablets (For instance vitamin D3, 2 pills of 10 µg, HEMA) can be advised. The patient information letter will encourage patients to get advice from their treating physician, general practitioner or dietary advisor.

All clinical chemical variables will be determined by the standard operating protocols of the Chemical and Haematological Laboratory of the Orbis Medical Center in Sittard. The vitamin D values will be determined by radioimmune assays following the standard operating protocols of the Chemical Laboratory of Maastricht University Medical Center in Maastricht. All vitamin D metabolite levels will be determined in the same run, using the same batch of radionucleotide.

The cellular assays are performed following the standard operating protocols of the experimental immunology laboratory of the Maastricht University Medical Center, according to the procedures used in study (NL 22666.096.07).

In short, peripheral blood mononuclear cells (PBMC's) will be isolated directly from heparinised blood by Ficoll gradient. Phenotypical analysis will be performed by intracellular and surface Flow Cytometry.

#### 6.4 Withdrawal of individual subjects

Subjects can leave the study at any time for any reason if they wish to do so without any consequences. The investigator can decide to withdraw a subject from the study for urgent medical reasons.

#### **6.4.1 Specific criteria for withdrawal (if applicable)**

Subjects will be withdrawn from the study if any of the following events occur:

- The reference values for serum total calcium are 2.10–2.55 mmol/L. If the serum total calcium level exceeds 2.55 mmol/L, the patient has to stop vitamin D supplementation until the measurement has been repeated. If the serum calcium level repetitively exceeds 2.55 mmol/L, the patient is withdrawn from the study. If not, the patient can continue the study.
- If liver- or kidney-function worsens clinically significant at week 6 when compared to baseline values, the patient will be withdrawn from the study and has to stop vitamin D supplementation immediately.

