#### **6.6 Follow-up of subjects withdrawn from treatment**

Subjects withdrawn from treatment, will have their safety measurements repeated at 2 weeks and 8 weeks after withdrawal from the study, to assess if their calcium levels normalise. The  $T^{1/2}$  of 25(OH)D is approximately 30 days.

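### Section 6.4.1 lets a calcium value taken off product decide an on-treatment safety event, conflicts with 5.3, and leaves on-treatment exceedances uncounted

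*Protocol*

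**What the plan says.** Section 6.4.1 gives 2.10–2.55 mmol/L as the reference range for serum total calcium and sets out three steps.

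- Hold: after one value over the upper limit, "the patient has to stop vitamin D supplementation until the measurement has been repeated".
- Withdrawal: this follows only when the limit is passed again.
- Continuation: for all other cases the rule reads "If not, the patient can continue the study".

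It gives no interval to the repeat, and it ties no calcium test to the restart.

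Other sections bear on the same event:

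- **5.3** places the pathological level above 2.60 mmol/L. If hypercalcaemia occurs, supplementation must stop, and "Normalisation of serum calcium will be fastened by applying calcium-free nutrition, and promoting an excessive fluid intake". It mentions neither a repeat test nor resumption.
- **6.3** schedules blood controls during supplementation at weeks 2, 4 and 6, then at week 12, when supplementation ends.
- **6.6** has withdrawn patients' "safety measurements repeated at 2 weeks and 8 weeks after withdrawal from the study, to assess if their calcium levels normalise".
- **6.7** ends the study when more than 2 patients have a hypercalcaemia or a liver or kidney problem, with a reference back to 6.4.1.
- **8.1** reports biochemical values as continuous variables, with medians and minimum–maximum ranges and no cut-off points. **8.2** tests values before against after treatment.

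**The concern.** The first high value is measured on product and the value that settles the matter is measured off product. If the product caused the rise, calcium should fall once it is stopped, and 5.3 and 6.6 both treat normalisation after stopping as the course to look for. A normal repeat is therefore compatible with a laboratory or biological outlier and equally with real toxicity that is resolving. Section 6.4.1 handles both in the same way: the patient may continue.

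Safety and tolerability of this dose are a stated secondary objective (section 2), and hypercalcaemia is the risk the protocol names. At stake is whether the final report can say how many of the 15 patients went above the calcium limit while taking the product, and whether those applying 6.7 would agree on what to count.

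**Working it through.** The protocol states no figure on this point that could be reproduced. The check is mainly a comparison of sections, followed by arithmetic that shows what can and cannot be sized.

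**1. Sections side by side**

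| Question | 5.3 | 6.4.1 | 6.7 |
|---|---|---|---|
| Calcium level | above 2.60 mmol/L | above 2.55 mmol/L | none of its own |
| Action | stop; no resumption mentioned | hold, repeat, then withdraw or continue | end the study at 3 or more patients |
| Single or repeated value | not stated | repeated, for withdrawal | not stated |

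No section says which takes precedence.

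**2. What the repeat can show.** A first value of 2.56 mmol/L needs a fall of (2.56 − 2.55)/2.56 = 0.4% to reach the limit. A value of 2.60 needs 0.05/2.60 = 1.9%, and 2.70 needs 0.15/2.70 = 5.6%. Close to the limit, a very small change decides between withdrawal and continuation.

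**3. How much exposure remains at the repeat.** Section 6.6 says that the half-life "of 25(OH)D is approximately 30 days". Assuming first-order decay, the fraction left after d days is 2^(−d/30):

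- 7 days: 85%
- 14 days: 72%
- 28 days: 52%

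These figures describe 25(OH)D. The protocol does not relate its rate of fall to that of calcium. They show only that the meaning of the repeat depends on an interval the protocol leaves open.

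**4. After the restart.** Events at weeks 2 and 4 are followed by a scheduled control two weeks later. After an event at week 6 the next is at week 12, a gap of 6 weeks.

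**5. What the report would contain.** A minimum–maximum range shows that at least one patient reached an extreme value, but not how many exceeded 2.55 mmol/L. A before–after comparison need not use the value that triggered a hold at week 2, 4 or 6. As written, section 8 yields no count.

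**6. Termination rule, for illustration only.** Suppose that 6.7 counts only events still present at the repeat. Let p be the true on-treatment event risk and c the share that normalises during the hold. The chance of termination is then P(X ≥ 3) with X ~ Binomial(15, p(1 − c)).

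| p | c = 0 | c = 0.3 | c = 0.5 |
|---|---|---|---|
| 0.10 | 18% | 8% | 4% |
| 0.20 | 60% | 35% | 18% |
| 0.30 | 87% | 64% | 40% |

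Both p and c are assumptions; the protocol supplies neither.

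**The case against.** Holding product while a test is repeated is a sensible precaution. The trigger is the upper reference value itself and lies below the level that 5.3 calls pathological, so some single values just above it are to be expected without toxicity. This stands: the hold is not the error.

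A reader might infer that the repeat is taken under calcium-free nutrition and high fluid intake. The documents do not say so. Those measures belong to 5.3, which applies once hypercalcaemia has occurred and provides no resumption; 6.4.1 does not mention them.

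A reader might also infer that a patient could go through hold and restart at every visit without ever meeting the withdrawal condition. That is only one reading. The repeated-exceedance wording can also cover a second high value at a later visit.

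Nor do the documents show that the rule hides events from the safety data. Adverse events observed by staff or reported by patients are recorded (7.2), the raw values stay in the data set, and an extreme value would widen the range. There are further safeguards: extra calcium checks when symptoms are reported (5.3) and withdrawal by the investigator for urgent medical reasons (6.4). With 85% of 25(OH)D left at 7 days, a prompt repeat is still taken under substantial exposure. None of this produces a count of patients above the limit or settles what 6.7 counts.

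Finally, it is tempting to ask that every single exceedance count towards termination. That would be a clinical stopping rule with a cost of its own. Assume that 2.5% of toxicity-free values exceed the limit and that there are four independent draws. Then 1 − 0.975^4 = 9.6% of patients would be counted, and the chance of 3 or more in 15 is 17% with no toxicity at all. With 1% of values above the limit it is 2%. This objection is accepted, and no such change is asked for.

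**Conclusion.** The point holds as a defect of definition and reporting. An off-product value at an unstated interval decides how an on-treatment event is handled. Section 6.4.1 does not agree with 5.3 on the level or on stopping versus resuming. Section 6.7 can be read either way on a value that normalised during the hold, partly because its reference to 6.4.1 may qualify only liver and kidney function. Section 8 plans no count of patients above the limit.

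A reader might go further and conclude that the rule systematically clears real toxicity or makes termination too rare. The documents do not support that. They give no event rate and no share of events that normalise, and 5.3 describes the risk as very low. The tabulated termination probabilities show the direction under the reading that only persistent events count; they do not estimate an effect in this trial.

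**What to change.** 1. In section 8 and in the safety report, list and count every patient with an on-treatment calcium above the limit. For each, give the first value, the repeat value, the date of the repeat and whether the patient was on or off product when it was taken. Record a normal off-product repeat as resolved on interruption.
2. Reconcile 5.3, 6.4.1 and 6.7 on three matters: the calcium level that defines the event, whether supplementation stops or may resume, and whether a single or a repeated exceedance counts towards termination. The clinical rule is for the sponsor to set; the need is that the sections agree.

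The cost is protocol wording and one event category on the case report form, with no added staff. The drawback is that some isolated borderline values will appear in the reported count. Listing each with its repeat lets the reader judge them.
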